### 2.6. Outcomes Assessment (Visits #1 and #2)

#### 2.6.1. Primary Outcome

*Modified Strandness treadmill walking test.* During this test, the walking speed is held constant (2 mph, i.e., 3.2 km/h) and the slope is fixed at 10% [18]. The participant is encouraged to walk for the longest time possible. The treadmill walking test is discontinued at the participant’s request, or by protocol, up to a maximum exercise duration of 20 min. A scale of pain (0 = no pain; 1 = onset of pain; 2 = moderate pain; 3 = intense pain; 4 = maximal pain) is used to quantify the appearance and development of pain during the walking test as well as pain relief during recovery [19]. Participants indicate the start of their claudication pain, from which the PFWD is computed, and the test stops at the point when the participant does not want to continue owing to lower limb pain, from which the MWD is computed. A 12-lead electrocardiogram monitors heart rate and cardiac electrical activity during the exercise-test procedure. In the Rennes center alone (due to equipment availability), gas exchange is assessed using a metabolic cart (MasterScreen CPX [MSCPX], Jaeger^®^, Germany). The system is calibrated according to the manufacturer’s instructions before each treadmill test.

To our knowledge, the minimal clinically important difference in the Strandness MWD has not been defined among patients with PAD. In MWD measurements obtained from a standardized graded maximal treadmill test (Gardner-Skinner walking test) among patients with PAD [20], a small clinically meaningful change was defined as ~107 m (i.e., 121 s) while a large clinically meaningful change was defined as ~214 m (i.e., 241 s).

#### 2.6.2. Secondary Outcomes

*Questionnaires.* The walking impairment questionnaire (WIQ) is used to assess the degree of functional impairment reported by the participants for different walking tasks. The WIQ is a valid tool to detect improvement or deterioration in the daily walking ability of participants with intermittent claudication [21,22]. The higher the WIQ score, the better the participant’s functional walking ability. The quality of life of the participants is assessed by the SF36 and by the Peripheral Artery Questionnaire (PAQ). The SF36 includes 36 questions that yields an eight-scale score of well-being and functional health, and two psychometrically based physical and mental health summary measures [23]. Each scale is directly transformed into a 0–100 scale on the assumption that each question carries equal weight. The lower the score, the greater the disability. The higher the score, the lesser the disability, i.e., a score of zero is equivalent to maximum disability and a score of 100 is equivalent to no disability [23]. The PAQ is a 20-item questionnaire that quantifies participants’ physical limitations, symptoms, social function, treatment satisfaction, and quality of life [24]. Its clinical validity has been confirmed in 711 patients with PAD [25]. Finally, dietary habits of participants are evaluated by a validated food frequency questionnaire to assess the diet associated with atherosclerotic diseases [26].

*Ankle-brachial index.* Measurement of ABI is performed according to American Heart Association recommendations [27] using a hand-held Doppler probe (8 MHz; Basic Atys Medical, Soucieu en Jarrest, France).

*Exercise transcutaneous oxygen pressure measurement (Exercise TcPO_2_).* This measure is performed only in equipped centers and aims to estimate the degree of ischemia during the modified Strandness treadmill walking test [7,28,29]. TcPO_2_ assessment detects regional blood-flow impairment at the proximal and distal limb simultaneously and bilaterally during exercise. The measurements from the TcPO_2_ electrodes allow the calculation of the DROP index (expressed in mmHg) and the absolute change in TcPO_2_ from resting value in each of the four limb electrodes, corrected for the absolute change in TcPO_2_ at the chest electrode [28,30].

*6 min walking test.* This test has been widely used in clinical trials in people with PAD to assess walking performance [8,31] and is performed according to standard procedure [31,32]. Among patients with PAD, following supervised and home-based exercise programs (pooled data), a small clinically meaningful change was defined as 12 m and a large clinically meaningful change was defined as 34 m [20]. From the study of the test–retest reliability of the 6 min walking test, Sandberg et al. [33] reported a minimal detectable change of 46 m.

*Daily PA level and walking pain experience.* Following both visits, the daily PA level of PAD participants is assessed over a consecutive 7-day period. We use a combination of PA monitors to progress in the knowledge of PA monitoring in PAD. Following both visits, during a consecutive period of seven days (excluding a preliminary day for habituation), participants are asked to wear a waist belt (right hip) holding two monitors: an accelerometer wGT3X (wGT3X+/wGT3X-BT models; Actigraph, Shalimar, FL, USA) and a GPS receiver (Qstarz BT-Q1000XT (Qstarz International Co., Ltd., Taipei, Taiwan). In addition, participants wear an accelerometer ActivPAL™ (ActivPAL4, PAL Technologies©, Glasgow, Scotland) adhered to the middle of the right thigh with a fixing system (Tegarderm^®^). A StepWatch pedometer is also worn at the right ankle level. Initially, participants wore the StepWatch 3.0 (OrthocareInnovations, Oklahoma City, OK, USA) but its non-rechargeable and non-replaceable battery had a limited life span. Thus, participants are now wearing the new 4.0 model (Modus Health™ LLC, Edmonds, WA, USA) during the protocol. The participants are carefully instructed to wear the monitors throughout the day for seven consecutive days and to remove the monitors during water-based activities (e.g., showering and swimming) and at bedtime; the exception is the activPAL4 that can be worn during showers and during the night. All the instructions for wearing the monitors are summarized in a handbook (File S3) that is sent to the participants together with the monitors. Participants are asked to report their bedtime and waking time every day in the handbook. In addition, at the end of each day, the participants report the main indoor and/or outdoor activities carried out throughout the day with a timestamp (File S3). Data from accelerometers will be processed following previously published procedures [34,35]. The main metrics computed to assess daily PA level will be the following: mean time per day of total PA; mean time per day of light, moderate, and vigorous PA; mean number of steps per day; mean number of steps per day (or mean daily stepping time) accumulated in different duration bouts; and mean number of steps per day (or mean daily stepping time) accumulated in different cadence bands.

Finally, to objectively quantify the pain experienced by participants during daily life walking, participants wear a watch on the wrist (right or left) and are asked to press event marker button(s) to indicate events related to walking-pain manifestations and stops induced by walking pain (File S3). The procedure has been previously described and validated [36]. Initially, the Micro Motionlogger^®^ watch (WatchAmbulatory Monitoring, Inc., Ardsley, NY; firmware Action-W version 2) was used at the beginning of the protocol but was progressively replaced by a new and more ergonomic home-based App developed on Android™ and deployed on Wear OS smartwatches (Huawei Watch GT or Fossil Carlyle, File S3). During the 7-day free-living PA measurement, an SMS is sent every morning to remind participants to wear the PA monitors. After the 7-day PA monitoring, participants send back monitors and the PA guide by mail using a prepaid package.

*GPS-measured outdoor walking capacity.* During the 7-day free-living PA measurement, participants are asked to complete two 30 min outdoor walking sessions while wearing and using the PA monitors as described above. The instructions to perform the walk were previously reported [37,38,39] and are summarized in the handbook (File S3). Data from the GPS receiver will be directly analyzed to process indicators of walking capacity, as previously reported [36,37,38,39]. For each participant, the main GPS parameters recorded will be: the total distance walked over the outdoor session; the whole duration of the outdoor session; the number of walking and stopping bouts; the mean walking speed calculated over each walking bout; the total time and distance over each walking bout; the total time over each stopping bout; the bout with the highest time and distance walked; and the mean time and distance over all the walking bouts. By combining the information recorded on the watch and GPS data, the outdoor PFWT and MWT will be computed [36]. Since the outdoor walking capacity depends both on walking speed and grade, the metabolic equivalent of task per min (MET·min) will be computed for each walking bout using previously published predictive equations for walking metabolic rate [40,41].

*Skin microvascular function assessment.* This measure is also performed only on participants included in Rennes due to device availability. Skin microcirculation is measured with the LSCI to assess the modifications of endothelial function at calf and forearm levels [42]. The skin microvascular function is measured after a fasting period. Two different tests are performed: The post-ischemic reactive hyperemia (PORH) and the local thermal hyperemia tests. The PORH test assesses the increase in skin blood flow to tissue that follows the release of a brief 3 min arterial occlusion [43]. The cuff is inflated at a supra-systolic pressure (50 mmHg above the systolic pressure). The PORH test, which is expected to be endothelium dependent and involving both myogenic and metabolic factors, evaluates the reperfusion of the vascular beds and is characterized by a peak in the skin blood flow after the cuff release [42]. Local thermal hyperemia is obtained with a special probe (42 °C–44 °C) that leads to a sustained increase in skin blood flow that is biphasic: an initial peak that is axon-reflex mediated, and a sustained plateau phase that depends on nitric oxide [44]. The LSCI was preferred to the laser Doppler flowmetry due to a better reproducibility [45]. Skin blood flow is expressed in arbitrary units or as multiples of the baseline.

### 2.7. Sample Size

The calculation of the number of participants per group was based on the expected improvement in the MWD after 12 weeks in the intervention group (NMES) compared with the control group. Considering previous studies [12,14] that assessed the effects of NMES during a program of lower duration (1 month), we expected a 50% improvement in MWD in the NMES group with no significant change in the CONT group. We assumed a baseline MWD of ~115 ± 78 m in both groups. Thus, considering a between-groups difference of approximately 58 m with a standard deviation of 78 m at the end of the 12-week program, the minimum number of participants to be included in each group is approximately 29, with an alpha risk of 0.05 and a power of 80%. We anticipated that the total number of participants to be included could be 80 (40 per group), allowing for a maximum ~30% dropout rate.

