### 2.5. Primary and Secondary Outcomes

Details are presented in File S1 (Item 2b). The primary outcome of the ELECTRO-PAD study will be the change in MWD at 12 weeks as assessed by a modified Strandness treadmill test (see outcomes assessment).

Secondary outcomes will be changes at 12 weeks in: (i) treadmill pain-free walking distance (PFWD); (ii) 6 min total walking distance; (iii) global positioning system (GPS)-measured outdoor walking capacity; (iv) ankle-brachial index (ABI); (v) daily PA level, including walking pain-manifestation assessment (see below); (vi) walking impairment questionnaire (WIQ) sub-scales and total scores; (vii) short-form health survey (SF36) score; (viii) peripheral artery questionnaire (PAQ) score; (ix) dietary questionnaire score; (x) delta from resting oxygen pressure (DROP) using TcPO_2_ during treadmill walking test and (xi) skin microvascular function assessed both at the forearm and calf levels using the laser speckle contrast imaging (LSCI) technique; and (xii) maximal walking distance according to the location of the arterial obstruction (using scan images).

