### 2.8. Data Collection, Management, and Analysis

*Data collection and management.* The data collected are in an electronic Case Report Form (eCRF) and data monitoring is carried out on a regular basis (~every six months).

*Statistical analysis (see also File S1, item 20a).* Descriptive statistics will be performed to describe the baseline characteristics of interest at the level of the two groups and for the different outcomes. Continuous data will be expressed as mean +/− standard deviation or median values with interquartile range, depending on the distribution. A normality test will be carried out to judge the Gaussian or non-Gaussian distribution of the data of the continuous variables studied. Two-sample, two-sided t-tests (or Mann–Whitney U test) and χ2 tests will be used to compare continuous and categorical characteristics of participants across the two groups at baseline, respectively.

For statistical analysis of the primary and secondary outcomes after study completion, two -sample, two-sided t-tests (or Mann–Whitney U test if the data is not normally distributed) will be used to compare changes in outcomes between baseline and the 3-month follow-up between the NMES and the CONT groups. However, in case of imbalance in baseline characteristics between the 2 groups, outcome data will be analyzed using linear regression models adjusting for significantly different baseline data between the two groups [46].

Firstly, an intention-to-treat analysis will be performed. As recommended [47], a missing at random (MAR) assumption will be made for missing data for principal analysis by performing complete cases and multiple imputation analysis. Deviation from MAR will also be assessed with sensitivity analysis under the missing not at random (MNAR) assumption, using controlled multiple imputation with different controlled scenarios. A per-protocol analysis will be also performed considering only participants with data available both at visit #1 and visit #2.

A subgroup analysis will be performed to explore the potential association between change in treadmill MWD and reported walking activity changes during the follow-up. In the NMES group, potential association between the total dose of NMES over the program and change in treadmill MWD will be assessed.

Statistical analysis will be carried out using R software [48]. The level of significance will be fixed at *p* < 0.05.

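### The sample size uses the SD of walking distance, but the primary test is on change in walking distance; no correlation is given, so the power of the planned test is not established

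*Protocol article*

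**What the plan says.** Section 2.7 starts from the baseline: "We assumed a baseline MWD of ~115 ± 78 m in both groups". It expects a 50% gain under NMES and no significant change in controls, and so sizes the trial on "a between-groups difference of approximately 58 m with a standard deviation of 78 m at the end of the 12-week program". At an alpha of 0.05 and 80% power it concludes that "the minimum number of participants to be included in each group is approximately 29". It then anticipates that "the total number of participants to be included could be 80 (40 per group), allowing for a maximum ~30% dropout rate".

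The quantity to be tested is set elsewhere. Section 2.5 states: "The primary outcome of the ELECTRO-PAD study will be the change in MWD at 12 weeks". Section 2.8 says that "two-sided t-tests (or Mann–Whitney U test if the data is not normally distributed) will be used to compare changes in outcomes" from baseline to three months. Regression adjustment appears there only as a response to baseline imbalance, and only for baseline variables that differ significantly between the groups.

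**The concern.** The SD entered in the calculation describes MWD at a single time point. It is the baseline value, carried forward to week 12. The planned test uses each participant's difference between two visits, and the spread of that difference depends on how strongly the two measurements correlate. Section 2.7 gives neither an SD of change nor a correlation, so its 80% power is not tied to the test described in Section 2.8. If the result is null, a reader could not tell whether the planned test had power well below or well above 80%.

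The dropout allowance is a lesser matter. The stated worst case takes each group slightly below the section's own minimum.

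**Working it through.** **Inputs (protocol article).** Difference 58 m (50% of 115 m is 57.5 m), SD 78 m, alpha 0.05, power 80%, minimum 29 per group, 40 per group with up to about 30% dropout (all Section 2.7). Two-sided two-sample test on change (Section 2.8). The correlation ρ between baseline and 12-week MWD is not given; 0.3 to 0.7 is an assumed range.

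**1. The plan's own figure.** Normal approximation: n = 2 × (1.96 + 0.8416)² × 78² / 58² = 28.4, so 29 per group (28.9 with 57.5 m, also 29). The stated 29 is reproduced. For the t-test itself (noncentral t) the answer is 29.4, so 30.

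**2. SD of the tested quantity.** With the same SD at both visits, as the plan assumes, SD(change) = 78 × √(2(1 − ρ)). This equals 78 m only at ρ = 0.5. The 58 m difference itself carries over: with equal baseline means and no control change, the group difference in change equals the group difference at week 12.

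Power for 58 m with 28 per group, the number left after 30% dropout, and the evaluable number per group needed for 80% power (both noncentral t):

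| ρ (assumed) | SD of change, m | Power at 28 per group | n per group for 80% |
|---|---|---|---|
| 0.3 | 92.3 | 64% | 41 |
| 0.4 | 85.4 | 70% | 36 |
| 0.5 | 78.0 | 78% | 30 |
| 0.6 | 69.8 | 86% | 24 |
| 0.7 | 60.4 | 94% | 19 |

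**3. Dropout.** 40 × 0.70 = 28, against a minimum of 29. Keeping 29 of 40 allows 1 − 29/40 = 27.5% dropout. Keeping the 30 that the t-test needs allows 1 − 30/40 = 25%. Working forward, 29/0.70 = 41.4, so 42 per group. At SD 78 m, t-test power is 78.0% with 28, 79.5% with 29 and 80.8% with 30 per group.

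**4. Adjusting for baseline MWD.** In a linear model with baseline MWD as covariate, the residual SD is 78 × √(1 − ρ²), whether the response is 12-week MWD or change. With 28 per group (53 residual degrees of freedom) and 58 m:

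| ρ (assumed) | Residual SD, m | Power at 28 per group |
|---|---|---|
| 0.3 | 74.4 | 82% |
| 0.5 | 67.5 | 88% |
| 0.7 | 55.7 | 97% |

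Under the plan's equal-SD assumption, this analysis stays above 80% across the range even at 30% dropout.

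**The case against.** **The dropout shortfall is rounding.** Every figure in that sentence is hedged. By the normal approximation that yields 29, the unrounded need is 28.4, and 28 per group gives 79.5% power. The 78.0% figure also reflects the move to the t-test. This objection largely stands: the gap is one participant per group and about 1.5 power points, so it is a wording correction and not the main point.

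**The SD may be adequate or even cautious.** This is also true: 78 m is right for change at ρ = 0.5 and conservative above it. A reader might infer from the 64% entry that the trial is underpowered. The document does not support that, because it gives no ρ and the range runs as high as 94%. What remains is that the section labels 78 m as the SD of distance and offers nothing to link it to change.

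**The full protocol may state the correlation.** It may, and the absence of ρ from a condensed article would not be a fault by itself. But the article does state which SD it used and which variable it tests, and the two do not match.

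**A 50% gain could widen the NMES arm.** A reader might take the gain as proportional for each participant, which would raise that arm's 12-week SD to 1.5 × 78 = 117 m and lower power further. Section 2.7 describes a group-level improvement and holds the SD at 78 m. Individual proportional gain is therefore an added scenario and is not used here to size the problem.

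**Quoting power for an adjusted model would create a new mismatch.** It would, if the analysis stayed as written. The adjusted-model figures apply only if the primary analysis changes as well.

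**Conclusion.** The concern holds in a limited form. The calculation is arithmetically sound for a comparison of 12-week MWD with SD 78 m, but that is not the planned primary test. For the change-score t-test with 28 per group, power is about 64% to 94% over ρ = 0.3 to 0.7, and it is close to the stated 80% only near ρ = 0.5. These figures assume equal SDs of 78 m at both visits and a true difference of 58 m; the range for ρ is assumed. The direction of the error cannot be determined, so the sample size cannot be called too small.

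Secondarily, 40 per group supports 29 completers up to 27.5% dropout and 30 up to 25%. At 30% dropout the plan's own inputs give about 78% power. The discrepancy is real but small.

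**What to change.** No extra enrolment is needed.

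- **Preferred.** Make the primary analysis a linear model of 12-week MWD (or change) adjusted for baseline MWD in all cases, not only after an observed imbalance. Restate Section 2.7 for that model with a stated ρ or a range: about 82%, 88% and 97% power at 28 per group for ρ = 0.3, 0.5 and 0.7 under equal SDs.
- **If the change-score test is kept.** Restate power from an SD of change, giving ρ and its source, or show the range.
- **In either case.** Correct the dropout sentence so that it matches the calculation it accompanies. For the plan's own calculation, that means about 25–27% tolerated dropout for 80% power, or about 78% power at 30%.

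The cost of the preferred option is an amendment to the primary analysis in Section 2.8, made and dated before outcome data are compared by group, plus restated figures in Section 2.7. Baseline MWD is already measured at visit 1, so nothing new is collected. Keeping the change-score test costs only the restated figures.

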### 2.8. Data Collection, Management, and Analysis

*Data collection and management.* The data collected are in an electronic Case Report Form (eCRF) and data monitoring is carried out on a regular basis (~every six months).

*Statistical analysis (see also File S1, item 20a).* Descriptive statistics will be performed to describe the baseline characteristics of interest at the level of the two groups and for the different outcomes. Continuous data will be expressed as mean +/− standard deviation or median values with interquartile range, depending on the distribution. A normality test will be carried out to judge the Gaussian or non-Gaussian distribution of the data of the continuous variables studied. Two-sample, two-sided t-tests (or Mann–Whitney U test) and χ2 tests will be used to compare continuous and categorical characteristics of participants across the two groups at baseline, respectively.

For statistical analysis of the primary and secondary outcomes after study completion, two -sample, two-sided t-tests (or Mann–Whitney U test if the data is not normally distributed) will be used to compare changes in outcomes between baseline and the 3-month follow-up between the NMES and the CONT groups. However, in case of imbalance in baseline characteristics between the 2 groups, outcome data will be analyzed using linear regression models adjusting for significantly different baseline data between the two groups [46].

Firstly, an intention-to-treat analysis will be performed. As recommended [47], a missing at random (MAR) assumption will be made for missing data for principal analysis by performing complete cases and multiple imputation analysis. Deviation from MAR will also be assessed with sensitivity analysis under the missing not at random (MNAR) assumption, using controlled multiple imputation with different controlled scenarios. A per-protocol analysis will be also performed considering only participants with data available both at visit #1 and visit #2.

A subgroup analysis will be performed to explore the potential association between change in treadmill MWD and reported walking activity changes during the follow-up. In the NMES group, potential association between the total dose of NMES over the program and change in treadmill MWD will be assessed.

Statistical analysis will be carried out using R software [48]. The level of significance will be fixed at *p* < 0.05.

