### 2.2. Recruitment, Randomization, and Blinding

Participants are being identified and recruited by the investigators from five French university hospitals located in the northwest (n = 4) and the southwest (n = 1) of France: Rennes (coordinating center), Angers, Brest, Caen, and Toulouse. In each center, participants are screened for eligibility during their usual medical appointment for PAD management, and during which a modified Strandness treadmill walking test (3.2 km/h, 10%) was performed to assess walking ability (see outcomes assessment). Eligible participants who meet the inclusion criteria (Table 1) were asked to participate in the study. A letter presenting the objectives and the protocol sequence is given to the participant (File S2) and, after ≥ a 48-h period, the participant is called by phone by a member of the local staff. If the participant agrees to participate, the inclusion visit (visit #1) is planned, preferably within the next 7 to 21 days (Figure 1). This strategy for participant enrolment is designed to: (i) minimize the burden of planning numerous inclusion visits (visit #1) while the potentially eligible participants had in fact a MWD > 300 m (exclusion criteria); and (ii) test the reproducibility of the treadmill walking test by assessing the variability of the MWD [17]. No inclusion percentage to achieve was given to each center. The enrollment period is anticipated to last ~43 months from study commencement (including enrollment of healthy participants in the second ancillary study).

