Inclusion and exclusion criteria for participants with PAD are displayed in Table 1. In addition, criteria for discontinuing allocated interventions are presented in File S1 (Item 11b). Participants provide paper-based written, informed consent before they participate in the study (File S2), which is collected by the assessor at visit #1 (inclusion visit, Figure 1). At visit #1, the order of the treadmill test and 6 min test is first randomized electronically, and the information is given to the assessor of the local center where the participant performs both tests accordingly. Once visit #1 is achieved, following an electronic process (File S1, Item 16a), each participant is randomized into one of the two arms (1:1) of the study: (1) NMES group; or (2) Control group (CONT). Randomization is performed as block randomization with a 1:1 allocation. The randomization is stratified and equilibrated (block for equilibration not provided here to preserve concealment allocation) in the five inclusion centers. Only the biostatistician, the data manager, and the research associate at the coordinating center have access to the allocation sequence to preserve the allocation concealment. In that way, the assessor of the different outcomes in each center is blinded to the participant treatment group allocation. The research associate of the coordinating center receives an email mentioning the participant group allocation. Then the research associate mails a box containing the following to the participant’s home:for both groups of participants: (i) a box containing the monitors for daily physical activity (PA) and outdoor walking-capacity assessment; (ii) a handbook that explains how to wear the monitors, how to perform the outdoor walking sessions, and that includes a diary to report different information (see below and File S3); (iii) a sealed envelope containing a brochure with advice for regular PA on a day-to-day basis (File S4).for the NMES group only: (i) an opaque box containing the NMES device; (ii) a sealed envelope containing the NMES handbook for implementation and follow-up of the NMES program (Files S5 and S6).

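### Randomisation is stratified by five centres but the fixed tests ignore centre, so the analysis is mildly conservative if centres differ in 12-week change

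*Protocol article*

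**What the plan says.** **Design (section 2.2).** "Randomization is performed as block randomization with a 1:1 allocation", and "The randomization is stratified and equilibrated (block for equilibration not provided here to preserve concealment allocation) in the five inclusion centers". Centre sizes are left open: "No inclusion percentage to achieve was given to each center".

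**Analysis (section 2.8).** For the primary and secondary outcomes, "two-sided t-tests (or Mann–Whitney U test if the data is not normally distributed) will be used to compare changes in outcomes"; each change is taken from visit #1 to the 12-week visit. Arms are also compared at baseline: t-tests or Mann–Whitney tests for continuous variables, and "χ2 tests will be used to compare continuous and categorical characteristics of participants across the two groups at baseline". If the arms are imbalanced at baseline, "outcome data will be analyzed using linear regression models adjusting for significantly different baseline data between the two groups".

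The article nowhere uses centre as a covariate or stratum in an analysis. Section 2.8 also refers to File S1, item 20a, which is not at hand.

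**The concern.** Stratified blocking forces the arms to be nearly equal in size within each centre, so differences between centres largely drop out of the treatment contrast. A pooled two-sample test does not know this and leaves between-centre variance in its error term. The adjustment rule cannot repair the mismatch, because it admits only variables that differ significantly between arms and the design prevents centre from doing so. The one factor singled out at randomisation is the one the rule shuts out.

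Centre could plausibly matter. Assessors are local, the treadmill test depends on effort, and test conditions vary: "In the Rennes center alone (due to equipment availability), gas exchange is assessed using a metabolic cart", and TcPO2 electrodes are used only in equipped centres. At stake are the accuracy of the reported standard error and some efficiency in a trial of 80 participants. Validity against false positives is not at stake.

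**Working it through.** **Inputs.** From section 2.7: difference 58 m, SD 78 m, two-sided alpha 0.05 (sidedness from section 2.8), power 80%, 29 per group, 40 per group randomised, maximum dropout about 30%. From section 2.2: five centres, 1:1 blocks, block size withheld. Assumptions: 78 m, stated for the end of the programme, is used as the SD of change; the share R of its variance that lies between centres is 0, 5, 10 or 20%.

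**1. The plan's own figure.** n per group = 2 × (1.960 + 0.842)² × 78² / 58² = 2 × 7.85 × 6084 / 3364 = 28.4, so 29. The stated 29 reproduces. Power at 29 per group is 80.8% by the normal approximation and 79.5% by the t distribution. At 40 × 0.70 = 28 completers per group it is 78.0% (t). The calculation has no centre term, so it agrees with the unadjusted test.

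**2. Can the rule admit centre?** With blocks of 4, a centre that stops mid-block is out of balance by at most 2. When the arms are about equal overall, a centre of size n with imbalance d adds about d²/n to the chi-square statistic. For centres of about 32, 12, 12, 12 and 12, the worst case is about 4/32 + 4 × 4/12 = 1.46, against a 5% critical value of 9.49 on 4 degrees of freedom. In simulation with block sizes 2, 4, 6, 8 and 10, and with equal or unequal centres, the chi-square test of centre between arms was significant in 0% of trials.

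**3. Size by formula.** Unadjusted SE = 78 × √(2/29) = 20.5 m. With centre in the model, SE = 20.5 × √(1 − R).

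| R | Adjusted SE (m) | Unadjusted / adjusted SE | n per group if adjusted |
|---|---|---|---|
| 0% | 20.5 | 1.00 | 29 |
| 5% | 20.0 | 1.03 | 27 |
| 10% | 19.4 | 1.05 | 26 |
| 20% | 18.3 | 1.12 | 23 |

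This ignores the 4 degrees of freedom and the balance lost through dropout.

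**4. Size by simulation.** N = 80, blocks of 4, centres 32/12/12/12/12, 27.5% random dropout (29/40 completing), total SD 78 m. Type I error is at a true effect of 0 m, power at 58 m.

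| R | Type I error, t-test | Power, t-test | Power, arm + centre |
|---|---|---|---|
| 0% | 5.0% | 78.9% | 77.8% |
| 5% | 4.6% | 80.1% | 80.4% |
| 10% | 4.3% | 80.3% | 82.1% |
| 20% | 3.8% | 81.8% | 87.0% |

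**5. Sensitivity.**
- Five equal centres: power 79.1 vs 77.9, 78.7 vs 79.3, 81.1 vs 82.9 and 81.5 vs 86.2% for the same values of R.
- At R = 20%, type I error of the t-test is 3.1% with equal centres and 2.8% with a 50/20/10/10/10% split. The Mann–Whitney test behaves alike (about 3.5 and 3.0%).
- At R = 20%, equal centres and no effect, the average reported SE is 20.5 m and the actual SE 18.8 m.
- At R = 10%, block sizes 2, 6, 8 and 10 give gains of about 1 to 3 points. Very unequal centres (48/16/8/4/4) narrow the gap.

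**The case against.** The strongest reply is that centre may matter little for this endpoint. The primary outcome is within-participant change, so a stable difference between centres in MWD level cancels, including one due to a metabolic cart used at both visits. The treadmill protocol is the same everywhere, the programme is done at home, and the coordinating centre's research associate contacts and instructs participants. The absence of centre quotas bears on centre size, not on outcome variation. This stands: R may be close to zero, where adjusting costs slightly more than it gains.

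A reader might infer that the reported error bars are simply wrong, or that power is lost in a trial with little to spare. The article does not support either. The first depends on a between-centre variance that it does not give. As to the second, the sample size was computed for the unadjusted comparison, and simulated power of that comparison stays between about 79 and 82% in the main scenario. What goes unused is extra efficiency, not planned power. Nor does a false-positive risk follow, since type I error is at or below nominal.

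File S1, item 20a, or a fuller analysis plan may add covariates. That limits any claim that centre is finally excluded. It does not change the article's wording, which names the tests and the only route to adjustment.

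**Conclusion.** The mismatch between design and analysis is in the text and is certain. Its consequence is conditional and probably modest. If centres differ in 12-week change, the unadjusted tests are conservative: at R = 10% the SE is about 5% too wide by formula, type I error is about 4.3%, and about 2 points of power are forgone; at R = 20% the figures are about 12%, 3.8% and 5 points. At R of 5% or less there is next to nothing to gain. The treatment estimate is not biased by this choice. These sizes rest on an assumed R, an SD of change of 78 m, dropout unrelated to outcome, and assumed block and centre sizes. The point does not apply to skin microvascular function, which is measured in Rennes only.

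**What to change.** In section 2.8, before database lock:

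- Make the primary analysis a linear model for 12-week MWD change with arm and centre as fixed terms, whatever the baseline tests show, and report the adjusted difference with its 95% CI.
- Do the same for secondary outcomes measured in more than one centre. Rennes-only outcomes are exempt.
- If a rank test is kept, use the centre-stratified van Elteren test in place of Mann–Whitney.
- Include centre in the multiple-imputation model.

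This is a change of wording and needs no new data or participants. The downside is 4 degrees of freedom, about 1 point of power if centres do not differ (78.9 vs 77.8%). Whether baseline MWD should also enter the model is a separate decision.
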